### Randomisation

At the end of the run-in period (2–3 weeks after visit 1), participants’ CGM data will be reviewed. A minimum of 10 days of data recorded, and less than 80% time in target glucose range, will be needed to proceed with randomisation. Eligible participants will be randomised in a 1:1 ratio to the use of HCL or to standard insulin therapy with CGM for 26 weeks. Randomisation will be done using a centrally administered web-based randomisation sequence with a permuted block design (block sizes 2 and 4) and will be stratified by site, age (≤30 years/>30 years) and baseline time in target glucose range (≤65%/>65%). Participants and investigators will not be masked to the intervention used during each period because of the nature of the interventions.

### Closed-loop group

Participants will use the CamAPS FX HCL system (Figure 2) comprising Dexcom G6 CGM (Dexcom, California, USA), YpsoPump insulin pump (Ypsomed, Burgdorf, Switzerland) and the mylife CamAPS FX app (CamDiab, Cambridge, UK) on a standard smartphone. Participants can use their own phone where compatible, or a compatible study smartphone will be provided online supplemental appendix.

**Figure 2 F2:**
[figure not shown]
CamAPS FX HCL system. In the present study, we used the CamAPS FX HCL system comprising: YpsoPump insulin pump (Ypsomed, Burgdorf, Switzerland); Dexcom G6 real-time CGM (Dexcom, California, USA) or other approved compatible CGM; smartphone hosting CamAPS FX app with the Cambridge model predictive control algorithm (University of Cambridge, Cambridge, UK) and communicating wirelessly with the insulin pump and CGM transmitter; and cloud upload system to review CGM/insulin data (Glooko, Göteborg, Sweden). The closed-loop algorithm is hosted within the CamAPS FX app which communicates wirelessly with the CGM device and insulin pump. CGM, continuous glucose monitoring; HCL, hybrid closed-loop.

Prior to starting HCL insulin therapy, participants will be trained on the use of the study insulin pump, study CGM and CamAPS FX app by the research team. Written guidance will also be provided. Competency on the use of the insulin pump, CGM and HCL system will be assessed. Further training may be delivered as required. Participants will use the HCL system for the next 26 weeks at home.

### Standard insulin therapy with CGM group (control intervention)

Participants will use the Dexcom G6 CGM. Prior to starting the standard insulin therapy with CGM, participants will be trained on the use of the CGM. Written guidance will also be provided. Competency on the use of study CGM will be assessed. Participants will continue their standard insulin therapy with the study CGM for the next 26 weeks at home.

### Contacts during 26-week study period

All participants will be contacted by email or telephone within 48 hours and at 1 week after initiation of the respective study arm. The purpose of this contact is to review the glucose and insulin data, troubleshoot any issues with the devices and record any adverse events or device deficiencies. Thereafter, participants will be followed up through study contacts (telephone/email) at monthly intervals to review glucose data, record any adverse events, device deficiencies, changes in insulin doses, other medical conditions and/or medication. Fasting (non-hypoglycaemic) C-peptide will be measured by dried blood spot completed at home at contact 3 and contact 5.

### Visits during the 26-week home study period

Study visits will occur at 3 and 6 months following initiation of the respective study arm. These study visits will take place at the clinical research facility, outpatient department or remotely if preferred. The purpose of these visits is to review glucose data; to record any adverse events, device deficiencies and changes in insulin doses; and to document other medical conditions and changes in medications. Additionally, a participant’s body weight, height and FEV_1_ will be recorded. Participants will be asked to complete questionnaires to assess quality of life and diabetes management. Participants will have a blood test for HbA1c and complete a fasting (non-hypoglycaemic) C-peptide dried blood spot. At the end of the final study visit, study devices will be collected, and participants will resume their usual diabetes care.

Throughout the trial, clinical care will be provided by the local diabetes/CF teams as per usual care. Participants and/or the clinical team are free to adjust insulin therapy as per usual clinical practice, but no active treatment optimisation will be undertaken by the study team.

### Participant withdrawal criteria

A participant may terminate participation in the study at any time without giving a reason and without any personal disadvantage.

The following prerandomisation withdrawal criteria will apply:

Participant time in range of >80% during the baseline masked CGM period.The participant is unable to demonstrate safe use of the CGM as judged by the investigator.

An investigator can stop the participation of a subject after consideration of the benefit/risk ratio. Possible prerandomisation and postrandomisation withdrawal criteria include:

Participant is unable to demonstrate safe use of study CGM and/or insulin pump as judged by the investigator.Significant protocol violation or non-compliance.Recurrent severe hypoglycaemia events related to use of the closed-loop system.Recurrent severe persistent hyperglycaemia unrelated to infusion site failure and related to use of the closed-loop system.Decision by the investigator or sponsor that termination is in the participant’s best medical interest.Allergic reaction to insulin.Severe allergic reaction to adhesive surface of infusion set or CGM.Serious adverse events.Pregnancy, planned pregnancy or breastfeeding.Technical grounds (eg, participant relocates).

## Study procedures

### Height and weight

Height and weight will be measured at the baseline visit, 3-month visit and end of study visit. Height will be measured in centimetres using a calibrated measuring device and weight will be measured in kilograms using a calibrated electronic scale.

### Forced expiratory volume in 1 s

Prebronchodilator FEV_1_ will be measured at the baseline visit, 3-month visit and end of study visit using an approved spirometer. The FEV_1_ for eligibility can be recorded within the past 6 months for the baseline visit. Measurements of FEV_1_ for the baseline visit, 3-month visit and end of study visit will be collected within 7 days of the visit using an approved spirometer.

### Blood samples

#### HbA1c

Blood samples for the measurement of HbA1c levels will be taken at the baseline visit, at 3 months and at the final study visit. HbA1c will be measured at a local laboratory using an International Federation of Clinical Chemistry and Laboratory Medicine-aligned method. HbA1c testing will follow the National Glycohemoglobin Standardization Program standards. Blood samples will be disposed of after analysis.

#### C-peptide

Capillary dried blood spot samples for the measurement of fasting (non-hypoglycaemic) C-peptide will be collected at baseline, at 1 month, 3 months, 4 months after randomisation and at the final study visit. Died blood spot samples for C-peptide will be stored deep frozen (−20°C or below) locally until analysis at a central laboratory (Core Biochemical Assay Laboratory, Cambridge, UK). Blood samples will be disposed of after analysis.

#### Glucose

Capillary blood glucose level will be measured just before the C-peptide blood sample is collected to exclude hypoglycaemia (<3.9 mmol/L).

### Masked CGM

During the run-in period, participants will wear a masked Dexcom G6 to collect baseline CGM data and to determine eligibility for randomisation.

### Psychosocial assessments

#### Questionnaires

Surveys used in this trial are listed in table 3. Surveys will be completed at the baseline visit, 3-month visit and end of study visit. Responses will be evaluated at the end of the study once all participants have completed the final study visit.

**Table 3 T3:** Human factors assessment

Questionnaire	Construct measured/relevant points	Timepoint
Problem Areas in Diabetes (PAID) Survey	20-item survey measuring diabetes-related emotional distress and covering a range of negative emotional problems of patients with diabetes.	Baseline, 3 and 6 months
Hypoglycaemia Confidence Survey	Includes 8 different common situations where hypoglycaemia occurs (eg, physical activity, driving) and evaluates the level of confidence in managing it in those situations (2 min).	Baseline, 3 and 6 months
INSPIRE Questionnaire	Survey developed for adults considering or actively using closed-loop. The 31 items cut across quality of life, benefits and burdens of using closed-loop (5 min).	Baseline, 3 months (closed-loop group only) and 6 months (closed-loop group only)
EQ-5D-3L	Developed to describe and value health across a wide range of disease areas. The survey consists of two pages: the EQ-5D descriptive system assessing 5 dimensions of health and the EQ-5D visual analogue scale (2 min).	Baseline, 3 and 6 months
Cystic Fibrosis Questionnaire-Revised (CFQ-R)	Disease-specific survey designed to measure the impact of cystic fibrosis on overall health, daily life, perceived well-being and symptoms. Developed specifically for use in people with a diagnosis of cystic fibrosis. It includes 50 items covering 9 quality of life domains (10 min).	Baseline, 3 and 6 months
Closed-loop experience questionnaire	Feedback questionnaire on closed-loop-specific experience, completed by participants being randomised to the closed-loop intervention arm (2 min).	6 months (closed-loop group only)

INSPIRE, Insulin Dosing Systems: Perceptions, Ideas, Reflections and Expectations Questionnaires-Adults .

#### Qualitative interviews

The qualitative evaluation will adopt a cross-sectional design in which (n=16–20) participants in the HCL arm will be interviewed once after they have at least 3 months’ experience of using the HCL system. Purposive sampling will be used to ensure diversity in terms of age, gender, CFRD duration and sociodemographic variables such as education, ethnicity and occupation. Interviews will begin by exploring participants’ lives and experiences of self-managing diabetes before using closed-loop, with a particular focus on the distinctive issues and challenges resulting from living with both CF and CFRD. The interview will then be used to explore whether and how using closed-loop has affected participants’ CFRD management experiences and everyday (work/school/family) lives.

### Patient and public involvement

Patients and the public were involved in the research from the very beginning in the development of this protocol. We worked in collaboration with the Cystic Fibrosis Trust to form a patient and public involvement (PPI) group which included people living with CFRD and relatives/caregivers of people living with CFRD. This group endorsed the primary endpoint (time in target glucose range) as being patient relevant and highlighted that research into interventions to reduce treatment burden was the top priority in the James Lind Alliance Priority Setting Partnership for CF at the time. The inclusion of the qualitative components to the trial was also endorsed by the PPI group. The PPI group has also been involved in other aspects of the trial design, including reviewing participant-facing study documents, inclusion and exclusion criteria and patient-relevant outcomes. One of the coapplicants of the study is a lay representative living with CFRD who has been involved in the study design from the outset. A person living with CFRD is a member of the Trial Steering Committee (TSC).

### Statistical analysis

All randomised participants with/without protocol violation and including dropouts and withdrawals will be included in the analysis according to intention-to-treat principle.

#### Primary outcome analysis

The primary analysis will evaluate the between-group difference in the proportion of time spent in the target glucose range of 3.9 and 10.0 mmol/L based on CGM levels during the 26-week intervention period.

The values will be compared using a linear mixed model; the dependent variable is the primary endpoint and the independent variable is treatment allocation, adjusting for baseline time in target glucose range, age and clinical centre. A 95% CI will be reported for the difference between the interventions based on the linear mixed model. Residual values will be examined for an approximate normal distribution. If values are highly skewed, then a transformation or robust statistical method will be used instead. A 5% significance level will be used to declare statistical significance for the primary comparison. A two-sided p value will be reported. The primary analysis will be a single statistical comparison of a single outcome measure.

#### Key secondary endpoints

Analysis of secondary endpoints will parallel the primary analysis. A transformation will be applied to all highly skewed secondary endpoints.

The following key and secondary endpoints will be assessed for between-group difference:

Proportion of time with sensor glucose >10.0 mmol/L (%) throughout treatment period.Mean sensor glucose (mmol/L) throughout treatment period.HbA1c (mmol/mol) at end of treatment period.

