##### Clinical endpoints (throughout the treatment period)

Change in fasting C-peptide (pmol/L).Change in body mass index (kg/m^2^).Change in percentage of predicted FEV_1_.Number of pulmonary exacerbations.Number of hospitalisations.

The Hochberg method will be used to adjust for multiple testing of secondary endpoints.

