### Safety analysis

For each of the following safety outcomes, mean±SD or summary statistics appropriate to the distribution will be tabulated by treatment group:

Number of severe hypoglycaemia events.Number of participants with any severe hypoglycaemia event.Number of adverse events per participant.Number of serious adverse events per participant.

All of the above safety outcomes will be tabulated for all participants (including dropouts and withdrawals), regardless of whether CGM data are available and irrespective of whether closedloop was operational. All serious adverse events will be listed for the entire study duration.

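### Two secondary event counts, pulmonary exacerbations and hospitalisations, fall under the primary linear mixed model, which suits counts poorly and takes no account of unequal follow-up

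*Protocol article*

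**What the plan says.** The Primary outcome analysis section of the protocol article defines the model: "The values will be compared using a linear mixed model; the dependent variable is the primary endpoint and the independent variable is treatment allocation". The covariates it names are time in range at baseline, age and centre. If the distribution is poor it adds: "If values are highly skewed, then a transformation or robust statistical method will be used instead".

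The Key secondary endpoints section carries this over, with one adaptation: "Analysis of secondary endpoints will parallel the primary analysis. A transformation will be applied to all highly skewed secondary endpoints".

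The Clinical endpoints section, within the other secondary efficacy endpoints, lists "Number of pulmonary exacerbations.Number of hospitalisations" over the treatment period, next to changes in C-peptide, body mass index and FEV1. It then places the secondary endpoints under a Hochberg adjustment, so formal tests are intended.

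The opening of the Statistical analysis section keeps dropouts and withdrawals in the intention-to-treat analysis, and the Sample size calculation section allows for 10% loss. The article gives no count model, rate, offset or person-time for the two counts. The sections with their own rules, on questionnaires and on safety, do not cover them.

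**The concern.** A linear model compares mean counts, or mean transformed counts. If most participants have no event, the data are a spike at zero with a short tail. A monotone transformation moves the spike but does not spread it. The resulting coefficient, such as a difference in mean log(1 + count), is not a quantity that a clinician can use.

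The model also treats every participant as observed for the same time. Someone who leaves after a few weeks without an event scores 0, the same as someone event-free for 26 weeks. If one arm loses more people, or loses them sooner, its mean count falls for that reason alone. The Participant withdrawal criteria section lists some possible reasons tied to use of the closed-loop system, so unequal withdrawal cannot be ruled out in advance. At stake are the estimates, and under marked imbalance the tests, for two clinical outcomes in the Hochberg family.

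**Working it through.** **The plan's own figure.** The article gives a sample size for the primary endpoint only, and nothing for the counts. With a difference of 5.0, SD 8.1, two-sided 5% and 90% power, the normal formula gives 2 × (1.960 + 1.282)² × 8.1² / 5.0² = 55.2, so 56 per arm. The exact t-test needs 57 per arm (power 0.904), or 114 in total. Then 57 / 0.90 = 63.3, so 64 per arm and 128 in total. Both stated totals reproduce.

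**Assumptions for the counts.** The article gives no event rate, dispersion or split of withdrawal between arms. Mean counts of 0.25, 0.5 and 1.0 per 26 weeks are assumed. Overall loss is held at the article's 10%, split as 10%/10%, 15%/5% or 20%/0% (closed-loop/control).

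**Share with no event.** Poisson: exp(−m). Negative binomial with dispersion 1: 1/(1 + m).

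| Mean m | Poisson | Negative binomial | Skewness of log(1 + count), simulated |
|---|---|---|---|
| 0.25 | 78% | 80% | about 1.9 |
| 0.5 | 61% | 67% | about 1.3 |
| 1.0 | 37% | 50% | about 0.8 |

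**Apparent ratio of counts when the true rate ratio is 1.** With a constant event rate, the expected count is proportional to mean follow-up. A proportion d withdrawing at uniform times leaves a mean follow-up of 1 − 0.5d. If all withdrawals fall in the first half, it is 1 − 0.75d.

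- 10%/10%: 0.95 / 0.95 = 1.00 (uniform); 0.925 / 0.925 = 1.00 (early).
- 15%/5%: 0.925 / 0.975 = 0.949 (uniform); 0.8875 / 0.9625 = 0.922 (early).
- 20%/0%: 0.90 / 1.00 = 0.90 (uniform); 0.85 / 1.00 = 0.85 (early).

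Reversing the 15%/5% split gives 1.054 and 1.085, so the direction depends on which arm loses more.

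**Simulation.** There were 1,500 trials per scenario, 64 per arm, with gamma-Poisson counts of dispersion 1. Unadjusted t-tests on raw and on log(1 + count) values stood in for the linear model. The comparator was an overdispersed Poisson model with a log follow-up offset. Rejection rates at nominal 5% under a true ratio of 1 are shown as raw / log / offset. The Monte Carlo standard error is √(0.05 × 0.95 / 1500), about 0.6 percentage points.

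| Mean | 10%/10%, uniform | 15%/5%, uniform | 20%/0%, early |
|---|---|---|---|
| 0.25 | 5.7 / 5.9 / 5.8 | 5.7 / 5.7 / 4.9 | 6.2 / 6.5 / 4.2 |
| 0.5 | 5.5 / 5.7 / 5.9 | 4.7 / 5.7 / 4.9 | 7.4 / 8.0 / 4.9 |
| 1.0 | 4.9 / 4.3 / 5.4 | 5.3 / 6.3 / 5.1 | 9.7 / 10.5 / 5.1 |

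The median rate ratio from the offset model was 0.99 to 1.02 throughout. At a true ratio of 0.6 with 10%/10% loss, power was similar for all three analyses: about 18–19%, 29–30% and 42–45% at the three means.

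**The case against.** The best case for the plan has four parts.

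- **Placement.** The rule stands under the key secondary heading, whose three endpoints are all continuous, while the counts stand under another. But the rule speaks of secondary endpoints without restriction and of all highly skewed ones. If it covered only the key three, the article would have no model for endpoints that it plans to test under Hochberg.
- **Flexibility.** To parallel is not to copy, and the primary analysis also allows a robust method. That is fair, but a robust method would still bring in no follow-up time.
- **Condensation.** An article may leave detail to an analysis plan. Silence would be no fault here, but the article names a model, and an analysis plan with a count model would depart from it.
- **Size.** With balanced withdrawal the linear analysis has near-nominal error and power like that of the count model. This stands, and it limits the weight of the point.

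A reader might also infer that the safety counts, such as "Number of adverse events per participant", share the fault. They do not: the Safety analysis section tabulates them with summaries suited to their distribution, without a model or a test. Person-time there would be a reporting preference.

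**Conclusion.** The concern holds in limited form. The stated rule puts two event counts through a linear model with no follow-up time. If events are infrequent, the estimate is hard to interpret whatever the pattern of withdrawal. Bias between arms is conditional: none with equal withdrawal, about 5% to 8% in the ratio at a 15%/5% split, and 15% at an extreme early 20%/0% split.

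A reader might infer that early withdrawal will bias the comparison, or that type I error is generally inflated. The article supports neither. It gives only an overall allowance of 10%, with 5–8% in earlier studies, and it lists the closed-loop withdrawal reasons as possible, with no frequency. Error stayed at 4.3% to 6.3% in the two milder simulated scenarios. Only the extreme one clearly raised it, to about 6% to 10%.

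The result rests on assumed event rates, dispersion and withdrawal splits. The high share of zeros is likewise an assumption, not something that the article reports. The simulation left out covariates and centre. Neither count is a primary or key secondary endpoint.

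**What to change.** State that the numbers of pulmonary exacerbations and hospitalisations are exempt from the rule that secondary analyses follow the primary one. Analyse each by negative binomial regression, or overdispersed Poisson regression, with log follow-up time as offset and the same covariates (baseline time in range, age, clinical centre). Report a rate ratio with its 95% CI, and take its p-value into the Hochberg procedure. Report withdrawals and total follow-up by arm beside the estimate, because the offset corrects for shorter observation only if withdrawal is unrelated to event risk.

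The cost is a few sentences in the analysis plan and a few lines of code. The article does not say that each participant's end of follow-up is recorded, so this should be confirmed; the regular contacts and visits make it likely. Completion is expected by August 2026, and the change should be made before outcomes are analysed by arm.

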#### Other secondary efficacy endpoints

##### Glycaemic endpoints (throughout the treatment period)

Proportion of time with sensor glucose <3.9 mmol/L (%).Proportion of time with sensor glucose <3.0 mmol/L (%).Proportion of time with sensor glucose >13.9 mmol/L (%).Proportion of time with sensor glucose in tight range of 3.5–7.8 mmol/L (%).SD (mmol/L) and coefficient of variation (%) of glucose to quantify the glucose variability.

##### Insulin endpoints (throughout the treatment period)

Total daily insulin dose (units/day).Total daily basal insulin dose (units/day).Total daily bolus insulin dose (units/day).

Trends in sensor glucose and insulin data collected within intervention arms will be evaluated on a monthly basis, and daytime (06:00 to 23:59) and overnight (00:00 to 05:59) glucose control will be evaluated separately.

##### Clinical endpoints (throughout the treatment period)

Change in fasting C-peptide (pmol/L).Change in body mass index (kg/m^2^).Change in percentage of predicted FEV_1_.Number of pulmonary exacerbations.Number of hospitalisations.

The Hochberg method will be used to adjust for multiple testing of secondary endpoints.

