**Trial registration number:**

NCT05562492.

STRENGTHS AND LIMITATIONS OF THIS STUDYThe study adopts an open-label, multicentre, randomised parallel design.The study includes a 26-week follow-up period with equal numbers of study visits between both groups.The study includes young people (≥16 years) and adults with cystic fibrosis-related diabetes, including transplant recipients to support generalisability of the findings.The comparator therapy reflects the current standard of care and includes insulin injections or non-automated insulin pump therapy with continuous glucose monitoring.The study includes both quantitative and qualitative psychosocial evaluation.

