### Inclusion criteria

The participant has CFRD requiring insulin therapy for >3 months.The participant is 16 years of age or older.Baseline time in target glucose range <80% during the run-in period.Forced expiratory volume in 1 s (FEV_1_) >30% of predicted mean for age, sex, race and height at the screening visit or within the past 6 months.Participant is willing to wear/carry study devices 24/7 (CGM/insulin pump/smartphone).Participant is willing to follow study-specific instructions.

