### Exclusion criteria

Any physical or psychological disease or condition likely to interfere with the normal conduct of the study or interpretation of study results as judged by the investigator.Commencement of CFTR modulator therapy within the previous 1 month.Previous solid organ transplant within the last 12 months or active on transplant waiting list.Use of closed-loop insulin therapy within the past 30 days.Known or suspected allergy to insulin.Severe visual impairment.Severe hearing impairment.Medically documented allergy or unable to tolerate the adhesive of plasters.Serious skin diseases at places of the body corresponding with CGM insertion sites.Participant is pregnant or breastfeeding or planning pregnancy within the next 12 months.

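### FEV1 change and pulmonary exacerbations are analysed with native and, by inference, transplanted lungs pooled, so the result has no single meaning for CF lung disease; a pre-specified native-lung analysis would supply one

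*Protocol article*

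**What the plan says.** - **Who is eligible.** The strengths and limitations list, printed under the trial registration number, describes the population as "including transplant recipients to support generalisability of the findings". The only transplant exclusion is "Previous solid organ transplant within the last 12 months or active on transplant waiting list". The lung-function criterion, FEV1 ">30% of predicted mean for age, sex, race and height at the screening visit or within the past 6 months", does not separate native from transplanted lungs. The article neither names lung transplantation nor gives an expected share.
- **Which endpoints.** The clinical endpoints include "Change in percentage of predicted FEV_1_.Number of pulmonary exacerbations", with no restriction by transplant status. They fall under the Hochberg adjustment for secondary endpoints.
- **Which model.** Under Key secondary endpoints: "Analysis of secondary endpoints will parallel the primary analysis". The primary model is a linear mixed model "adjusting for baseline time in target glucose range, age and clinical centre".
- **Which population.** "All randomised participants with/without protocol violation and including dropouts and withdrawals will be included in the analysis", on the intention-to-treat principle.
- **Randomisation.** The strata are site, age and baseline time in range. Transplant status is not among them.

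**The concern.** Including transplant recipients is sound for time in range, which has the same meaning in every participant. The two respiratory endpoints differ. After a lung transplant FEV1 describes the graft, and it can change for reasons unrelated to CF lung disease. Whether a pulmonary exacerbation is the same event in both groups depends on a definition that the article does not give.

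The Introduction links CFRD to pulmonary infection and declining lung function, and the Abstract names FEV1 change among the outcomes. Readers will therefore want to interpret these endpoints as evidence about CF lung disease. With the two groups pooled, a null result could reflect dilution and a positive one could reflect a few graft events. The trial is open-label, so a native-lung analysis chosen after the data are seen would carry little weight.

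**Working it through.** **1. The plan's own figure.** For a difference of 5.0 percentage points, SD 8.1, 90% power and two-sided 5%, the exact t-test needs 56.13 per arm, so 57 per arm or 114 in total (power 0.904). With 10% loss, 57/0.9 = 63.3, so 64 per arm or 128. The stated figures reproduce. They concern time in range only, and nothing below changes them.

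**2. Assumed inputs.** Neither of these is in the article:
- p, the share of lung recipients: 5%, 10% or 20%.
- d, the difference between recipients and others on the endpoint, in residual SDs: 0.5 or 1.

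All results use 57 per arm.

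**3. Chance imbalance.** At p = 10% there are about 11 recipients. If each is allocated 1:1 independently, the probability of a split of 8 to 3 or worse is 2(1 + 11 + 55 + 165)/2048 = 464/2048 = 0.227. An 8 to 3 split is a gap of 5/57 = 8.8 percentage points between arms, which moves the contrast by 0.088 × d SDs: 0.044 at d = 0.5 and 0.088 at d = 1. The standard error of the contrast is √(2/57) = 0.187 SD, so the shift is about 0.23 to 0.47 standard errors. More generally, the SD of the between-arm gap in share is √(2p(1−p)/57), which gives 4.1, 5.6 and 7.5 percentage points at p = 5%, 10% and 20%.

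**4. Precision.** Leaving out a binary term multiplies the variance by 1 + p(1−p)d². Take an effect that has 80% power with the term included:

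| p | SE increase, d = 0.5 | Power | SE increase, d = 1 | Power |
|---|---|---|---|---|
| 5% | 0.6% | 0.795 | 2.3% | 0.782 |
| 10% | 1.1% | 0.791 | 4.4% | 0.765 |
| 20% | 2.0% | 0.784 | 7.7% | 0.739 |

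The direction is not certain. If recipients' FEV1 change had half the SD of the others, then at p = 10% the variance factor would be 0.9 + 0.1 × 0.25 = 0.925 and pooling would multiply the SE by 0.96.

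Exacerbation counts were also simulated: 114 participants, overdispersed counts, an assumed 0.6 events per 26 weeks with native lungs and 0.1 after transplant, halved on closed-loop, and a linear model on log(1 + count). A transplant term alone changed the variance of the contrast by about 0 to 2% at 5% to 10% recipients and by about 2 to 4% at 20%.

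**5. Dilution.** If closed-loop had no respiratory effect in recipients, the pooled effect would shrink by the factor (1−p). Power is then Φ(2.80(1−p)/√(1 + p(1−p)d²) − 1.96). At d = 0.5 this gives 0.754, 0.703 and 0.594 for p = 5%, 10% and 20%. A transplant main effect in the model would not recover this, because the loss lies in the quantity being estimated.

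**The case against.** **Part of the adjustment may already be planned.** A parallel of the primary analysis can be read as adjusting each endpoint for its own baseline, as the Questionnaires section does for scores. Baseline FEV1 is then probably in the FEV1 model already, and analysing change removes much of any stable level difference between graft and native lung. This stands for FEV1. It supplies neither a transplant term nor, on its face, baseline FEV1 in the exacerbation model.

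**The detail may sit elsewhere.** Event definitions and subgroup or sensitivity analyses are commonly left to a full protocol or SAP, and neither is shown. This stands too: their absence from the article is not the point. The point is the analysis that the article does state, and if a native-lung analysis already exists, the sponsor need only confirm it.

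**Pooling follows from the stated aims.** Intention to treat and generalisability both favour one population, and the article's stated aim is glycaemic control, safety, experience and quality of life. This is a good reason to keep the all-randomised result. It does not make that result interpretable as an effect on CF lung disease.

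**Stronger readings.** A reader might infer that the respiratory comparisons are biased. They are not: allocation is randomised, and chance imbalance is part of the error that the confidence interval covers. A reader might also infer an appreciable loss of precision or power from the missing term. That rests wholly on assumed figures, is small under most of them, and could reverse.

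**Conclusion.** The point holds as one of interpretation. The eligibility criteria admit earlier solid organ recipients, and the two lung endpoints pool all randomised participants under a model with no transplant term. The contrast therefore has no single respiratory meaning if lung recipients are enrolled. That they are is an inference from the criteria, and their number is not given.

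The size depends on the assumed share. At 10% recipients there is a 23% chance of an 8 to 3 or worse split, worth up to about half a standard error at d = 1. If recipients do not respond, 80% power falls to about 70% at d = 0.5. With few recipients all of this is negligible. The documents show no fault in the hospitalisation endpoint on this ground, and they do not support a case for restratifying. Time in range, the key secondary endpoints and the sample size are untouched. This is a worthwhile refinement of two lower-tier endpoints, not a defect in the trial's main result.

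**What to change.** For change in percentage predicted FEV1 and number of pulmonary exacerbations only:

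1. Pre-specify an analysis in participants without a lung transplant, and state that any conclusion about CF lung disease rests on it.
2. Report it beside the all-randomised result, which stays as planned.
3. Include baseline percentage predicted FEV1 as a covariate in the exacerbation model, and confirm that it is in the FEV1 model.

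This needs wording only, fixed before results are seen. Transplant history must already be established to apply the exclusion criterion, medical history is taken at the baseline visit, and FEV1 is measured there.

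The cost is a smaller sample and a wider interval in the native-lung analysis. With equal variances the SE grows by 1/√(1−p): about 2.6%, 5.4% and 11.8% at 5%, 10% and 20% recipients. If the treatment effect were the same in recipients, the restricted analysis would be slightly less powerful than the pooled one. The case for it is interpretability rather than power.
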